### 8.3. Procedures set up for recording and reporting adverse events

#### 8.3.1. Characteristics of an adverse event

**Adverse event (AE):** any untoward or unfavourable medical occurrence in a human subject participating in biomedical research, whether that occurrence is connected or not to either the study or the experimental procedures carried out during the study.

A **severe adverse event (SAE)** meets one or more of the following criteria:

- Results in death;
- Is life-threatening (places the subject at immediate risk of death, at the time the event occurs, and this, independently of all consequences any corrective or palliative therapy might provide);
- Results in important or durable incapacity or handicap;
- Results in inpatient hospitalization or prolongation of existing hospitalization;
- Results in a persistent or significant disability or incapacity;
- Any alarming event (undesired clinical event or alarming laboratory result or that may be considered as such by the investigator).

**Side Effect (SE):** any harmful and undesirable reaction related to the strategy

**Serious Side Effect (SSE):** any serious and undesirable reaction attributable to the strategy.

**Unexpected Side Effect (USE):** any undesirable effect of which nature, severity, intensity or evolution is not concordant with information appearing in the investigator's brochure.

**Imputability:** relationship between an Adverse Event (AE) and the study's strategy. Any AE found to be related to the study's strategy will be thereafter considered as a **Side Effect (SE)**. Factors to be taken into account for the determination of imputability are:

- Timeline of events;
- The Adverse Event (AE) abates when the intervention is discontinued once the strategy has ended, and/or reappears upon a re-challenge with the intervention;
- Notion of a similar event having occurred during the strategy's implementation
- Existence of some other aetiology (causation).

**Intensity:** the severity of a given Adverse Event (AE) will be estimated by the investigator, according to the following classification scale:

- **Mild, level 1:** an Adverse Event that is generally transitory, with no impact on activities of daily living (ADL);
- **Moderate, level 2:** an Adverse Event annoying enough so as to incur moderate impact on ADL;

- **Major, level 3:** an Adverse Event that either incurs considerable impact on the participant's activities of daily living (ADL), or causes some form of invalidity, or constitutes a threat for the life of the participant.

Remark: Adverse Event *Intensity* should not be confused adverse event *Severity*, which serves as a guide to define the various reporting obligations and procedures.

### 8.3.2.Role of the investigator

#### 8.3.2.1. Reporting of severe adverse events (SAEs)

##### 8.3.2.1.1. *Information to be passed on to the sponsor*

Every SAE will be described on the form provided for that purpose ("Initial Report of a Severe adverse event" - « Déclaration Initiale d'Événement Indésirable Grave » or "Follow-up Report of a Severe adverse event" - « Déclaration de Suivi d'Événement Indésirable Grave ») all in trying to as most exhaustive as possible.

Information to be reported includes the following:

- Participant's Identification (number, code, date of birth, date of inclusion, sex, weight, height),
- Severity of the adverse event,
- Date (and time) of onset and end of the adverse event,
- Clear and detailed description of the adverse event (diagnosis, symptoms, intensity, chronology, actions - Initiated and various results obtained),
- Evolution of the adverse event,
- Participant's current diseases or relevant antecedents
- Treatments received by the participant,
- Link of causality of the adverse event with the simulation session, the eventual treatments been taken, the study itself, or with any other criteria.

Along with the adverse event report, the investigator should also include the following, whenever possible:

- A copy of the hospitalization report of (if the participant were to be hospitalized);
- A copy of the autopsy report, in the case of death;
- A copy of all the results of all complementary exams performed, including relevant negative results, by appending, as well, all the normal value ranges as provided by laboratory;
- Any other document that the investigator might consider as either useful or relevant.

These documents will be processed by making the participant's identity anonymous, using the participant's identification number alone.

##### 8.3.2.1.2. *Procedures for reporting a severe adverse event to the sponsor*

All SAEs, whatever their relation of causality with the present study (with the exception of those are listed in the protocol as not requiring any immediate reporting), must be reported:

- By [contact].

One can join the person responsible for the University Hospital of Poitiers Vigilance Center (Centre de Vigilance, Direction de la Recherche, CHU de Poitiers), [name] [name]:

- By call: [contact]
- By [contact]
- By email [[contact]](mailto:[contact])

##### 8.3.2.1.3. *Delay period for reporting to the sponsor*

All SAEs must necessarily be reported to the study's sponsor within **24 hours** of their onset (or as soon as the investigator physician has been notified).

The initial report may be followed by further relevant information either within **8 days** in the case of a fatal event or life-threatening prognosis, or within **15 days** in all other cases.

##### 8.3.2.1.4. *Time period for reporting to the sponsor*

The investigator has the responsibility to note and report all SAEs that may arise during the entire course of the study:

- Starting from the date of signature of the consent,
- Pursuing throughout the entire duration of participant follow-up foreseen by the protocol,
- And extending up to 4 weeks after participant follow-up termination.

[figure not shown]

#### 8.3.2.1.5. Specificities of the protocol

Severe adverse event not subjected to immediate reporting:

Certain circumstances requiring hospitalization may not actually arise from severity criterion "hospitalization" and, as such, should not be declared as severe adverse events

- Admittance for social or administrative reasons
- Hospitalization for routine treatment or surveillance of the studied pathology, and not associated to any deterioration of the participant's initial health state
- Hospitalization for scheduled medical or surgical treatment before the trial's start.

#### 8.3.2.2. Reporting of non-severe adverse events

All the other Adverse events will be reported on the form "Adverse event" (« événement indésirable ») included in the observation notebook, while noting the following: date of onset, description, intensity, duration, mode of resolution, aetiology, imputability and decisions taken.

### 8.3.3. Role of the sponsor

#### 8.3.3.1. Analyze severe adverse events (SAEs)

The sponsor should evaluate:

- **The causality of each SAE:** all adverse events, for which the investigator or the sponsor estimates that there exists reasonable argument in favour of a relation of causality with the study's strategy, will be considered as putative undesirable effects. In case of evaluation divergence between the sponsor and the investigator, the two opinions will be mentioned in a report that will be sent to the proper authorities, should such a report be necessary,
- **The expected/unexpected character of each SAE,** by using the most current reference document (brochure for the investigator)

#### 8.3.3.2. Scoring imputability

According to ICH recommendations on management of clinical trial adverse events - ICH E2B (R3), version of May 12, 2005 - an evaluation of imputability is to be performed for every SAE reported. The scoring method is as follows:

- **No relation:** the event appears in an incompatible timeframe period (delay) with regard to the study's implementation, and/or there is a sufficient information indicating that the observed reaction has no relation with the study, and/or there exists a likely alternative explanation.
- **Doubtful relation:** the event's chronology (appearance, evolution) is weakly compatible with regard to the study's implementation timeframe, and is apparently attributable to factors other than those of the study's strategy, such as the participant's clinical state, or the concomitant administration of other products.
- **Possible relation:** the event appears at a moment that is compatible with regard to the study's implementation timeframe, and could not reasonably be attributed to some other factor, such as the participant's clinical state, or the concomitant administration of other products. The evolution after study termination should also be compatible, and no other pharmacological or pathophysiological explanation should account for the event.
- **Highly plausible relation:** the event appears at a very suggestive moment within study's implementation timeframe, and could not reasonably be attributed to some other factor, such as the participant's clinical state, or the concomitant administration of other products. The evolution after study termination should also be compatible, and some pharmacological or pathophysiological explanation should account for the event.

Adverse events presenting a doubtful, possible, likely or highly likely relation with the study's strategy, should be considered as being connected to the trial. Should they be unexpected, they are to be qualified as Unexpected Adverse Events, and should be reported by the sponsor (cf. Following paragraph).

#### 8.3.3.3. Reporting Unexpected Serious Side Effects

The sponsor will declare all serious, unexpected side effects to the France's National Agency of Medication and Health Product Security ("ANSM - Agence Nationale de Sécurité du Médicament et des produits de santé"), to France's Protection Committee of Human Subjects (CPP - "Comité de Protection des Personne") and to the investigators. A statutory report will be made within a maximum delay of **7 calendar days** for all unexpected serious side effects. Any additional, relevant information must tracked, and be transmitted within a further maximum delay of **7 calendar days**.

#### 8.3.3.4. Annual transmission of safety reports

One year after the study's onset, the sponsor will write out a safety report that will include:

- A list of all serious side effects, expected or unexpected, susceptible to being connected to the study's strategy,
- A concise and critical analysis as to the safety of all participants who will lending themselves to this study.

This report can eventually be handed to the coordinating investigator for approval. It will be sent to both, the France's National Agency of Medication and Health Product Security ("ANSM - Agence Nationale de Sécurité du Médicament et des produits de santé") and France's Protection Committee of Human Subjects (CPP - "Comité de Protection des Personne"), within a delay of **60 days**, starting one year following the study's implementation onset.

#### 8.3.3.5. Reporting other safety data

This report will include any data concerning safety, or any new fact that could significantly modify the trial study's benefit/risk evaluation or that could lead to envisage modifications concerning study implementation. For example:

- A) Any clinically significant increase in the frequency of appearance of an expected serious side effect;
- B) Any suspicion of unexpected, serious side effect, that will have manifested itself in participants having already finished with the trial, and that will have been reported by the investigator or the sponsor, accompanied by any eventual follow-up reports;
- C) Every new fact concerning the progress of the clinical trial or the development of the study strategy, when this new fact is susceptible to pose a potential threat to the health and safety of the participants.
- D) The recommendations of the independent surveillance committee, if need be, if they are deemed to be relevant for the safety of the participants.
- E) Any unexpected serious side effect reported to the sponsor by another sponsor, of a clinical led in another country, and concerning the same not pharmacological intervention.

The sponsor must make a report to the France's National Agency of Medication and Health Product Security ("ANSM - Agence Nationale de Sécurité du Médicament et des produits de santé") and France's Protection Committee of Human Subjects (CPP - "Comité de Protection des Personne") as soon as possible, and at the latest within a delay of 7 calendar from the moment the sponsor has been informed. Any additional, relevant information must tracked, and be transmitted within a further maximum delay of **7 calendar days**.

#### **8.3.4. In utero exposure**

Pregnancy is not expected during the study (exclusion criteria). Any pregnancy should be declared at once to the sponsor.

The investigator should then inform the person responsible for the sponsor's Clinical Trial Pharmacovigilance Center (Pharmacovigilance des Essais Cliniques), and send a Serious Adverse Effect report by fax, that will include the predicted date of birth, as well as coordinates of the obstetrician and maternity ward that will be involved with delivery, should the pregnancy be continued.

The investigator should pursue patient follow-up until pregnancy comes to term, or is interrupted, and report the overall evolution to the sponsor.

Should the pregnancy's evolution be accounted for by the framework defining of severe adverse effects (miscarriage with hospitalization, foetal death, innate abnormality...) the investigator must then follow the procedure for reporting Severe Adverse Effects.

#### **8.3.5. Monitoring Committee**

#### **8.4. Participant follow-up procedures and duration following an adverse event**

Every adverse event will be followed until its complete resolution (stabilization at a level considered as acceptable by the investigator, or return to the initial state), even in the case the participant went out of the research.

### **9. STATISTICS**

Software utilised: software SAS version 9.0.

#### **9.1. Description of statistical methods intended for use, including intermediate analyses agenda**

##### **9.1.1.Descriptive analysis**

**Quantitative variables** (various scores, cortisol concentration values, participant heart rates, RR' intervals,...) will be described by the mean and standard deviation, or the median and interquartile intervals.

**Qualitative variables** (age, sex, professional status, years of professional experience) will be summarized by the actual samples size and corresponding percentages for each of the modalities.

##### **9.1.2.Evaluation of the effect of stress on performance**

The relationship between

- The various variables and indicators of stress (salivary cortisol concentration, Holter parameters of, scores from the various stress scales) evaluated during the 1-st session (basal stress) and during the following sessions,
- And performance (global performance, IO insertion and teamwork evaluation scores), evaluated during the latter sessions,

will be studied by calculating a Pearson correlation coefficient (or Spearman correlation coefficient if need be). This calculation will be realized on the entire study population as well as within each of the groups 1 and 2. A search for any sort of heterogeneity based on status (senior physician, junior physician, nurse, ambulance driver) will be undertaken, as well.

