##### **Psychological stress:**

will be assessed using 4 self-assessments:

- **Self-assessment** using STAI - *State-Trait Anxiety Inventory* (Spielberger 1983) just before and right after the simulation session, as well as following debriefing.
- Using **SOM self-rating scale** (Olpin 2010). For each self-assessment, participants will be placed in an isolated room so as not to be disturbed.
- **Early post-trauma stress disorder** will be determined on the 7th day following simulation, using IES-R - *Impact of Event Scale-Revised* (Brunet 2003), which will be emailed at that time to each participant.
- **Late post-trauma stress disorder** will be determined one month following simulation, using with PCLS - *Post-traumatic Check-List Scale* (Weathers 1993), which will be emailed at that time to each participant.

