#### 4.3.6. Debriefing

All the simulation sessions will be followed by a debriefing session, according to Rudolph's method of "*good judgment*" (Rudolph 2006, Rudolph 2008), and led by supervisors previously trained in this technique (University course Training at the University of Paris Descartes).

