##### 4.4.2.6. Number of salivary cortisol concentration measurements

Salivary cortisol concentrations will be measured the day before the session, then just before and just after simulation, as well as after debriefing that is 4 times per simulation session.

Group 1: 36 cortisol concentration measurements per participant

Group 2: 12 cortisol concentration measurements per participant

Total: 288 x 4 = 1152 cortisol concentration measurements

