### **6.1. Evaluation of the effect of stress on performance**

At first, we shall estimate the effect of **stress** on team **performance**, using three parts:

- By obtaining evidence of the existence of a biological, electrophysiological and psychological stress, during the progress of various scenarios;
- By estimating the impact of stress on global team performance (determined by degree of respect for the appropriate algorithm);
- By estimating the impact of stress on insertion of an IO access: insertion technique (evaluation scale), decision-making timing and duration;
- By estimating the impact of stress on teamwork: evaluation of leadership (evaluation scale) and communication (evaluation scale).

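### Section 9.1.2 correlates stress with performance as an effect of stress, without separating readings taken before or during the scenario from those taken after it

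*Protocol*

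**What the plan says.** Section 9.1.2 relates two sets of variables. The first is "The various variables and indicators of stress (salivary cortisol concentration, Holter parameters of, scores from the various stress scales", and these are "evaluated during the 1-st session (basal stress) and during the following sessions". The second is given as "And performance (global performance, IO insertion and teamwork evaluation scores), evaluated during the latter sessions". The relationship "will be studied by calculating a Pearson correlation coefficient (or Spearman correlation coefficient if need be". No sampling time within a session is chosen or ruled out. Because stress from the following sessions is included, the text admits pairs in which stress and performance come from the same session.

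The direction is stated elsewhere. The section heading speaks of an effect of stress on performance. Section 6.1 lists among its aims "By estimating the impact of stress on global team performance", and says the same for IO insertion and teamwork. The expected-results entry in the summary predicts that stress lowers team performance. Section 9.2 sizes the study on the stress-performance correlation.

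On timing, section 4.4.2.6 has cortisol taken "the day before the session, then just before and just after simulation, as well as after debriefing that is 4 times per simulation session", so the protocol counts the post-debriefing sample as part of the session. Section 4.3.6 states: "All the simulation sessions will be followed by a debriefing session". Under psychological stress in section 4.1, early post-traumatic stress "will be determined on the 7th day following simulation, using IES-R", and PCLS follows at one month. Section 7.3.2 treats the simulation itself as the trauma to which these two scales respond.

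**The concern.** A Pearson or Spearman coefficient is symmetric, so any direction has to come from time order, and section 9.1.2 does not fix one. A reading taken after debriefing cannot have influenced the performance already scored in that session. The reverse is possible: a session that went badly may leave its members more stressed. If such readings are pooled with earlier ones, a negative coefficient would be reported as an impact of stress when it could equally show the impact of performance.

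At stake is the directional conclusion in section 6.1 and in the expected results. Correct handling of team clustering or of repeated sessions would not restore the time order.

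**Working it through.** **1. The plan's own figure.** Section 9.2 gives r = 0.50, two-sided 5%, power about 90%, N = 48. By Fisher z, n = ((z for 1 - alpha/2 + z for power) / atanh r)² + 3 = ((1.960 + 1.282) / 0.549)² + 3 = 37.8, so 38. At N = 48 the power is 95.8%. The stated 48 is therefore not reproduced, but nothing below depends on that.

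**2. Time order.** Marks per session in the section 4.4.1 schedule, where performance is marked only in the simulation column:

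| Measure | Before | During scenario | Right after | During debriefing | After debriefing | 1 week / 1 month |
|---|---|---|---|---|---|---|
| Cortisol | 2 | 0 | 1 | 0 | 1 | 0 |
| Holter | 2 | 1 | 1 | 1 | 2 | 0 |
| BP/HR | 2 | 0 | 1 | 0 | 1 | 0 |
| SOM | 1 | 1 | 0 | 0 | 0 | 0 |
| STAI | 2 | 0 | 1 | 0 | 1 | 0 |
| IES-R | 0 | 0 | 0 | 0 | 0 | 1 |
| PCLS | 0 | 0 | 0 | 0 | 0 | 1 |
| Total | 9 | 2 | 4 | 1 | 5 | 2 |

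After the scenario: 4 + 1 + 5 + 2 = 12 of 23 (52%). Leaving out IES-R and PCLS: 10 of 21 (48%). From debriefing onward: 1 + 5 = 6 of 21, or 8 of 23 with the two late scales. These are schedule marks, not planned analyses. Section 7.3.2 places SOM after the simulation, which differs from the schedule; the count follows the schedule.

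**3. Which pairs are affected.**
- First-session stress against later-session performance: stress comes first. One reservation is that first-session readings taken after the scenario may reflect first-session performance, and so carry lasting team ability into the correlation.
- Same session, just-before reading: stress comes first.
- Same session, Holter during the scenario: concurrent with performance, so direction is not settled.
- Same session, right-after reading: later than performance, but plausibly a marker of stress during the scenario.
- Same session, post-debriefing reading, IES-R or PCLS: later than performance and, since every session is debriefed, also later than debriefing began.

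**4. Illustration of size.** Assume stress has no effect on performance and performance shifts later stress with correlation r. The protocol gives no value for r; -0.3 to -0.5 is an assumption. The chance of a significant result is approximately Phi(atanh|r| × sqrt(n - 3) - 1.960).

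| \|r\| | n = 12 | n = 48 |
|---|---|---|
| 0.3 | 0.310 × 3 = 0.929, giving 15% | 0.310 × 6.708 = 2.076, giving 55% |
| 0.5 | 0.549 × 3 = 1.648, giving 38% | 0.549 × 6.708 = 3.685, giving 96% |

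A simulation with 48 independent pairs (8,000 trials per setting, no pre-scenario effect, later stress built from pre-scenario stress, performance and noise) gave 55%, 82% and 96% for reverse correlations of -0.3, -0.4 and -0.5. The same test on pre-scenario readings stayed at 4.6% to 5.3%.

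**The case against.** The strongest reply is that section 9.1.2 speaks of a relationship, uses a symmetric coefficient and designates no predictor, and that the choice among sampling times is often left to a statistical analysis plan. That is fair as to missing detail. It does not answer the stated direction: the protocol names the stress indicators without distinguishing their timing and calls the exercise an evaluation of the effect, and section 6.1 of the impact, of stress.

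Other points stand and limit the finding:
- A reader might infer that IES-R and PCLS are certainly in the correlations. The words about indicators evaluated during a session can be read to leave out scales e-mailed 7 and 28 days later. The post-debriefing physiological and STAI readings do not depend on that reading.
- A reader might infer that every reading after the scenario should go. Section 4.1 targets stress during the simulation, and section 2.4 describes salivary cortisol as raised during or right after an event. No cortisol, BP/HR or STAI is scheduled within the scenario, so the right-after values are its nearest markers. Just-before values partly measure anticipation.
- A reader might infer that teams are told they performed badly. Section 4.3.6 names a debriefing method and does not say that scores or verdicts are disclosed.
- Reverse influence is also possible for Holter during the scenario, and team ability could drive both stress and performance even with pre-scenario readings. Restricting the timing removes one route to a false directional claim, not all of them.

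**Conclusion.** The point holds for same-session pairs. Section 9.1.2 does not separate readings that precede or accompany performance from those that follow it, and a negative correlation based on post-debriefing readings (or on IES-R and PCLS, if included) cannot support the claim that stress lowers team performance.

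A reader might go further and conclude that the whole stress-performance analysis is invalid, or that the trial carries a 55% to 96% risk of a false finding. The documents support neither. The lagged first-session pairs are in the right order, and the percentages rest on an assumed reverse correlation. The upper range also needs 48 independent pairs, whereas section 4.2.1 describes performance as team performance and there are 12 teams, for which the illustrative range is 15% to 38%. The time-order argument itself rests on no assumed figure. This is an inexpensive correction to the analysis text that leaves the design, sample size and data collection unchanged.

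**What to change.** Amend section 9.1.2 as follows.
- Exclude post-debriefing readings, IES-R and PCLS from the same-session stress-to-performance correlations, and report them as consequences of the session. The Holter segment recorded during debriefing belongs with them.
- Base the same-session effect analysis on just-before readings and on Holter during the simulation, stating that the latter is concurrent with performance.
- Keep right-after cortisol, BP/HR and STAI as markers of stress during the scenario, reported as associations without direction.
- Keep first-session stress against later-session performance, noting that first-session readings taken after the scenario may carry lasting team ability.

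No new data are needed. The cost is that fewer correlations support the effect statement, and that those resting on just-before values partly describe anticipatory stress.

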##### 4.4.2.3. Number of individual simulation sessions :

Group 1: 6 teams x 4 members per team x 9 sessions = 216

Group 2: 6 teams x 4 members per team x 3 sessions = 72

TOTAL = 216 + 72 = 288 individual simulation sessions

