#### **7.3.2. Quantification of stress**

Quantification of stress will make use of various tools and particular attention:

- Salivary samples for cortisol concentration measurements will be taken one day before the simulation session (at approximately 18H00), the day of the simulation session, just before and right after the simulation session - and preceding as well as following - the debriefing session. Tubes will be preserved in a refrigerator allocated for that purpose in the Simulation Laboratory, and then be sent to the Biochemistry laboratory of the University Hospital of Poitiers (CHU de Poitiers) for analysis ([name] and [name]).
- A Holter device will be placed on each of the male participants by [name], and on each of the female participants by [name], the day before the simulation session (at approximately 18H00). The Holter device will be worn for a total duration of 24 hours. Since the simulation sessions will take place between 14H00 and 15H00 in the Simulation Laboratory, the Holter device will remain in place during 3 hours following the simulation session's end. The recording cassettes will be removed, collected and read once a week in the cardiology department of the University Hospital of Poitiers (CHU de Poitiers) ([name] and [name]).
- A non-invasive measurement of blood pressure will be made the day before the simulation session (at approximately 18H00), the day of the simulation session, just before and right after the simulation session - and preceding, as well as following - the debriefing session. Every measure of blood pressure will be associated to a timely measure of the participant's heart rate.
- Quantification of psychological stress will make use of three questionnaires and SOM score after simulation:
  - SOM: is a score between 0 and 10 obtained by self-assessment after simulation sessions

- STAI is a self-assessment questionnaire, used for estimating both basal and induced, acute stress. Participants will fill out the questionnaire in an isolated room, the day before the simulation session (at approximately 18H00), the day of the simulation session, just before and right after the simulation session - and preceding, as well as following - the debriefing session.

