##### **9.1.3.Evaluation of performance score variations**

Variations in global team, IO access, and teamwork performance scores will be estimated in terms of temporal sequence. In each of the groups 1 (9 sessions) and 2 (3 session), score modifications between the various simulation sessions will be tested by means of an ANOVA for repeated measures (or the Friedman non parametric test, if need be).

Concerning the entire study population, linear mixed effects models (for continuous responses observed over time) will eventually be used envisaged so as to take into account, in a common analysis, the entire set of data collected throughout the various sessions, and, more notably, parameters involved in the development of stress management strategies compared to stress and repeated simulations.

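### Section 9.1.2 tests the stress-performance relationship with a plain correlation that ignores team, person and session, although only 12 teams supply the scores and the row unit is not stated

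*Protocol*

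**What the plan says.** Protocol 9.1.2 relates stress indicators, "evaluated during the 1-st session (basal stress) and during the following sessions", to performance: "And performance (global performance, IO insertion and teamwork evaluation scores), evaluated during the latter sessions". The relationship "will be studied by calculating a Pearson correlation coefficient (or Spearman correlation coefficient if need be"). The scope is stated next: "This calculation will be realized on the entire study population as well as within each of the groups 1 and 2". The only refinement is by profession: "A search for any sort of heterogeneity based on status (senior physician, junior physician, nurse, ambulance driver) will be undertaken, as well".

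Other sections bear on this:
- 9.2 names the stress-performance relationship as the main objective and sizes the trial on it: correlation 0.50, two-sided 5%, power about 90%, 48 subjects.
- 4.2.1 treats performance as team performance, with one global clinical score per team and session.
- 4.4.2.2 and 4.4.2.3 count 72 team sessions and the corresponding person-sessions: "TOTAL = 216 + 72 = 288 individual simulation sessions".
- 6.2 expects repetition to improve performance, and leaves open whether stress stays high or falls.
- 9.1.3, on performance score variations, mentions a model for repeated data: "linear mixed effects models (for continuous responses observed over time) will eventually be used envisaged so as to take into account, in a common analysis".
- 4.4.1 schedules some stress markers before, some during and some after the session. 9.1.2 does not say which time points enter the correlation.

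**The concern.** The standard test of a correlation assumes independent rows. Here the four members of a team share one global score in each session. Their stress in that session is likely to be alike because they face the same scenario together. If sessions are pooled, the same teams and persons also recur, up to nine times.

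Pooling brings a second problem. Repetition is the randomised intervention and is expected to change performance. If stress also changes with repetition, session number drives both variables, and they correlate even if stress has no effect on performance within a session.

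A third problem is timing. Cortisol and STAI are also sampled after the session and after debriefing, IES-R comes after 7 days and PCLS after about a month. A poor performance can raise these markers. At stake is whether a significant coefficient can be read as evidence on the trial's stated main objective.

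**Working it through.** **The plan's own sample size.** By Fisher's z, n = ((z₀.₉₇₅ + z₀.₉₀)/atanh(0.50))² + 3 = ((1.960 + 1.282)/0.549)² + 3 = 37.8, so 38. The stated 48 is not reproduced; it would give 95.8% power. That is a separate matter. What counts here is that the calculation treats each participant as one independent row.

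**Layout (4.4.2).** 6 teams × 9 sessions + 6 teams × 3 sessions = 72 team-sessions; × 4 members = 288 person-sessions, of which 216/288 = 75% come from group 1.

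**Assumptions (none given in the protocol).**
- Moderate clustering: team share of performance variance 0.3; stress variance shares of team 0.1, person 0.3, team-session 0.1.
- Higher clustering: team share of performance 0.5; stress shares 0.2, 0.3, 0.1.
- Linear trends of 0, 0.5 or 1 SD over the year.
- No true effect of stress in any setting, and one score shared by the four members.

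**Reading 1: one session, 48 persons.** Within a session the performance scores of team members are identical (correlation 1). Their stress values correlate 0.1 + 0.1 = 0.2. The variance of r is inflated by about 1 + (4 − 1) × 1 × 0.2 = 1.6. The nominal 5% test then rejects with probability 2 × [1 − Φ(1.96/√1.6)] = 12%. Simulation gives 11-13%. Under higher clustering the factor is 1 + 3 × 0.3 = 1.9 and the rate about 16% (also 16% simulated). If stress is not alike within teams, the rate stays near 5%.

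**Reading 2: 288 rows pooled** (4,000 simulated trials per setting; the row marked * comes from a separate run of 6,000)

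| Setting, no stress effect | Mean r | Significant at 5% |
|---|---|---|
| No trend, no clustering beyond the shared score | 0.00 | 4.8% |
| No trend, moderate clustering | 0.00 | 23% |
| No trend, higher clustering | 0.00 | 39% |
| Performance alone rises 1 SD, moderate clustering | 0.00 | 22% |
| Stress −0.5 SD, performance +0.5 SD, no clustering | −0.03 | 9% |
| The same, moderate clustering* | −0.03 | 26% |
| Stress −1 SD, performance +1 SD, moderate clustering | −0.11 | 50% |
| Stress +1 SD, performance +1 SD, moderate clustering | +0.11 | 49% |

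A separate simulation of moderate clustering without trend gave 21%, hence the range of about 21-39% for clustering alone.

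**Check on the shift in r.** With time scaled 0 to 1, its variance is 0.104 over nine equally spaced sessions and 0.167 over three. Pooled, this is 0.75 × 0.104 + 0.25 × 0.167 = 0.120. Opposite trends of 1 SD give r = −0.120/(1 + 0.120) = −0.107. Trends of 0.5 SD give −0.030/(1 + 0.030) = −0.029. Both agree with the simulation.

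**Comparator.** An analysis of the 72 team-session rows, with team and session effects fitted, rejected in 4.6-5.5% of null trials in every setting. Team was a fixed effect in this check.

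**The case against.** The strongest reply is that 9.1.2 never says person-sessions are pooled. Section 4.4.2.3 counts sessions and does not define an analysis set; the only analysis n in the protocol is 48, one row per person. A reader might infer a 288-row analysis, but the text does not establish it. This stands, so the pooled figures are conditional. It does not rescue the test, because the 48-person reading also exceeds 5% under moderate clustering.

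A reader might also infer that repeated rows by themselves create a correlation. They do not: without trends in both variables the mean r stays at 0, and clustering only makes significance too easy to reach.

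Nor does the protocol predict falling stress, so it cannot be said that the bias must favour the expected finding that stress lowers performance. If stress rises, the spurious r is positive.

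A spurious r of about 0.1 is also small beside the target of 0.50. The risk is a misleading p-value rather than a false effect of the size sought.

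On timing, pre-session cortisol, STAI, blood pressure and heart rate, and Holter recordings during the session, are collected too. Session-1 stress set against performance in later sessions cannot be caused by that later performance. The reverse-direction problem is therefore confined to markers taken after the scored session. For SOM the timing is unclear: 4.4.1 marks it before and during simulation, whereas 7.3.2 says it is "obtained by self-assessment after simulation sessions".

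Finally, 9.1.3 already contemplates mixed models on all sessions. They are optional, stand under a different analysis, and do not bind 9.1.2.

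**Conclusion.** The concern holds in this form: the method named in 9.1.2 does not fit the design on either reading, and the row unit is left open. Under moderate assumed clustering the nominal 5% test rejects a true null in about 11-13% of trials with 48 persons in one session. With 288 pooled rows, clustering alone gives about 21-39%. Pooling also shifts r if both variables trend, by about 0.03 for 0.5 SD trends and 0.11 for 1 SD trends, in a direction the protocol leaves open.

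That team, person and session are ignored follows from the text. The size of the error rests on assumed variance shares and trends, and ranges from none (no stress clustering, no trends) to about 50% significant in the settings tabulated. The Spearman fallback changes none of this, since it assumes independent rows as well.

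**What to change.** In 9.1.2:
- State the analysis unit.
- Make a mixed model the main stress-performance analysis, with session number and group as fixed effects and team as a random effect. Use degrees of freedom suited to 12 teams.
- Analyse team scores at team-session level. Enter team-mean stress, and in separate analyses the stress of each professional status, so that the planned status comparison is kept. Add a random person effect only where individual rows are used.
- Use pre-session or in-session markers as explanatory variables. Keep markers taken after the session (post-session cortisol and STAI, IES-R, PCLS) for the reverse question.
- Report the stress slope with its confidence interval, worded as an association. Keep the correlation coefficient as descriptive only.

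Reconcile the timing of SOM between 4.4.1 and 7.3.2, and make the optional model in 9.1.3 consistent with the new text.

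The change needs analysis wording and programming only; apart from settling when SOM is taken, data collection is unaffected. The price is a less simple summary and wider intervals.
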